**Surgical procedures**

***Endoscopic evacuation***

In this intervention group, patients will receive endoscopic surgery under general anesthesia. A 4-5cm skin incision is made according to the position of hematoma on brain CT scan. The approaches include the middle frontal gyrus approach for anterior basal ganglia hemorrhages that are not elongated but rather are more spherical. A parietooccipital small boneflap is created to treat posterior basal ganglia and thalamic hemorrhages. In cases involving superficial lobar hemorrhages, use a small boneflap directly at the location where the lesion comes closest to the surface. Then make a bone flap about 2cm in diameter and incise the dura mater in a cruciate fashion. Use a new-developed endoscopic introducer (China National Invention Patent: 201210066281.1) to make an appropriate working channel for the endoscope. First, impale the blunt puncturing lever in a predetermined position and then pull out the inner core. Second, suck with a syringe to determine whether the puncture lever has been in the right place. After confirmation, place the transparent cannula along the puncture lever. Through the space made by the transparent introducer, we can carefully evacuate intracerebral hematoma under the surveillance of endoscope. Plasminogen activator (urokinase) will not be injected after endoscopic surgery.

***Stereotactic aspiration***

In the aspiration group, the target point was set at near the posterior edge of the hematoma chosen on CT scan image with the largest expansion of hematoma. First, the patient undergoes a brain CT scan with slice thickness <5mm and the CT image data in Digital Imaging and Communications in Medicine (DICOM) format will be collected. Available commercial neuro-navigation or free mobile-device-based navigation was recommended in all centers to improve accuracy of catheter puncture. The target point is chosen on the CT scan with the largest expansion of the hematoma and special attention was paid to stay away from important cortex function areas. Hematoma aspiration was done with a 10 mL syringe until first resistance. After confirmation of catheter by postoperative CT, urokinase of 30,000 units every 12h was injected through the catheter to dissolve residue hematoma for 3-5 days. Catheter was removed when there was no more blood drained or the catheter had been placed for up to 5 days.

***Small boneflap Craniotomy***

Patients in this group will receive hematoma evacuation by small boneflap craniotomy under general anesthesia. Well-trained neurosurgeons will decide the surgical approach according to hematoma location and size on CT scan. To minimize the damage to normal brain tissue, operative incision should be made as small as possible. After removing the bone and incise the dura mater, cut open the cortex to reach the hematoma on the basis of protecting functional cortex areas and blood vessels. The hematoma will be evacuated as much as possible with the help of operation microscope. After careful hemostasis, the blood pressure should be moderately elevated to confirm that there has been no bleeding site. Only when the brain tissue swells significantly after hematoma evacuation, the bone flap should be expanded and abandoned. When necessary, a catheter would be placed in the hematoma cavity though urokinase is not usually injected.

**Concomitant care and interventions**

All patients will be cared for in a neurosurgical intensive care unit (NICU) until they are considered stable enough to move to an intermediate care or general unit. Neurological status will be monitored in the NICU by GCS and hourly neurological evaluation, which includes vital signs, level of consciousness and limb muscular strength.

**Outcomes measurements**

The primary outcome of this study is the degree of disability estimated using the modified Rankin Scale (mRS) 6 months after ictus. An unfavorable outcome is defined as death or dependency with a mRS of 3-6. Living patients’ independence in activities of daily lives and quality of life will be a highlight of this study. We will also measure patients’ quality of life and their performance in activities of daily living using the Barthel Index at 6-months follow-up. Secondary outcomes also include: hematoma clearance rate evaluated at 72h after surgery, operation time, intraoperative blood loss, postoperative GCS score 7 days after surgery, rebleeding rate, days of NICU stay, intracranial infection rate during hospitalization, 1 month mortality, 3 months mortality, hospitalization expenses, and Barthel Index at 6 months.

**Data collection and follow-up**

A special case report form (CRF) with detailed record rules has been developed in order to ensure accurate data collection. Patients’ personal data are made anonymous and numbered by the system. A list of patient names and study numbers is kept in a separate file to ensure that patients’ confidentiality is maintained. Demographic, clinical and neurological data are recorded at the time of enrolment and throughout follow-ups. The filled CRFs should be sent to trial secretary expeditiously.

Copies of the CT scans at enrollment, 1 day, 3 days and 7 days after surgery will be sent to the trial secretary together with the CRFs. All CT data should be in DICOM compatible format. DICOM images are sent anonymously with only patient identifier visible. The images will be analyzed by trained readers blinded to treatment group and patient identifier. In the past studies, hematoma volumes are calculated almost all by the ABC/2 formula. However, there’s significant estimation error using the ABC/2 formula to calculate hematoma volume, especially in large irregular hematomas. In this trial, we will use a precise and free method, the software 3D Slicer to measure both preoperative and postoperative hematoma volumes (Figure 2).

[figure not shown]

Figure 2 Hematoma volume measurement with software 3D Slicer. a. preoperative brain CT scan confirmed left external capsule hemorrhage; b. automatic depiction of the hematoma using threshold effect; c. 3D reconstruction and volume measurement of hematoma.

Follow-up data will be collected at 1 month, 3months, and 6 months after onset. All patients are encouraged to make a regular return visit to the hospital. Patients who cannot make a regular return visit will be followed-up through telephone or postal questionnaires. Our goal is to achieve at least 90% follow-up by means of full cooperation of all the investigators.

**Statistical analysis**

Statistical analysis will be on a “intention to treat” basis. Measurement data will be described using mean and standard deviation or median and interquartile range while count data will be described using indexes such as percentage, ratio and relative risk. The primary analysis will be a simple categorical frequency comparison using the Chi-squared test for prognosis based favorable and unfavorable outcomes at 6 months. The continuous variables will be analyzed by One-way ANOVA. Logistic regression analysis will be undertaken for age, gender, hematoma volume, preoperative GCS, surgical method, and intracranial infection. All statistical analyses will be performed using SPSS statistics 26.0 (IBM Corp. USA). A value of two side P <.05 was considered statistically significant.

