**Methods/design**

**Objectives**

This trial primarily aims to investigate whether and to what extent endoscopic evacuation and stereotactic aspiration could improve the outcome of supratentorial HICH compared with small boneflap craniotomy. This trial will also help to better define the indications for different surgical methods and help to determine the best surgical method for treatment of supratentorial HICH. Another objective is to evaluate the separate effects of different surgical treatments on patients’ independency and activities of daily living.

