**Sample size and randomization**

***Sample size***

It was reported that the rate of unfavorable outcome of patients receiving craniotomy with a supratentorial hematoma volume >30 ml was 49% to 67% and minimally invasive surgeries might decrease the rate of unfavorable outcome by about 8% to 22% compared with craniotomy. Our recent retrospective study showed that endoscopic surgery lowered the risk of unfavorable outcome in patients with supratentorial HICH by nearly 28% in comparison with craniotomy. We assume that the endoscopic surgery and stereotactic aspiration could reduce the risk of unfavorable outcome from 33% to 21%. A sample size of 720 (240 in each group) would be required to show a 12% benefit from minimally invasive surgery with 90% power and a type I error probability of .05 with a 10% dropout rate taken into consideration.

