***Randomization***

To minimize selection bias and accidental bias, Patients were randomly allocated to endoscopic evacuation group, aspiration group, or small boneflap craniotomy group in 1:1:1 ratio using a central randomization system based on computer-generated number sequence after a written informed consent was signed. Neither the neurosurgeons nor the patients could know the grouping beforehand. Randomization must take place within 24 hours of ictus and patients will be operated on within 12 hours of randomization. During the randomization process the neurosurgeon is informed of the treatment group the patient is allocated to and should record this. Best medical treatment must begin as soon as possible and continue throughout follow-up in all patients.

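### The primary Chi-squared test does not fix which of the three arms it compares, and no ungated reading of it both answers the technique-specific objective and keeps the stated type I error of .05

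*Protocol*

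**What the plan says.** Three places in the protocol bear on this.

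- **Objectives.** The primary aim is to investigate "whether and to what extent endoscopic evacuation and stereotactic aspiration could improve the outcome of supratentorial HICH compared with small boneflap craniotomy". A further aim is that the trial will "help to determine the best surgical method for treatment of supratentorial HICH". The first implies two comparisons with a shared control; the second implies a third, between the two techniques.
- **Sample size.** Unfavorable outcome is assumed to fall from 33% to 21% with both techniques. The text then says: "A sample size of 720 (240 in each group) would be required to show a 12% benefit from minimally invasive surgery". The benefit is thus attributed to minimally invasive surgery as a class. The design values given there are a type I error of .05, power of 90% and dropout of 10%.
- **Statistical analysis.** "The primary analysis will be a simple categorical frequency comparison using the Chi-squared test for prognosis based favorable and unfavorable outcomes at 6 months". The only decision rule is "A value of two side P <.05 was considered statistically significant". The groups entering the test are not named, and no order, gate or adjustment is given.

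Under Randomization, patients are allocated to "endoscopic evacuation group, aspiration group, or small boneflap craniotomy group in 1:1:1 ratio".

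**The concern.** Which arms the primary test compares is a design decision: it determines what a significant result means, how many patients are needed and what the error rate is. Here the objective is specific to each technique, the sample size speaks of minimally invasive surgery as one entity, and the test names no groups. Three readings are open: one 3x2 table, minimally invasive surgery pooled against craniotomy, or separate 2x2 tables.

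At stake is the primary conclusion. A significant three-group or pooled result could be reported as support for both techniques when only one is better than craniotomy. A set of separate tests could be reported at .05 when the chance of a false claim is larger. If the contrast is still open when the data are seen, the choice between readings can follow the results.

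**Working it through.** **Inputs.** Rates 0.33 (craniotomy) and 0.21 (each technique), two-sided alpha .05, power 90%, dropout 10%, 240 per group: all from Sample size. Evaluable per arm: 240 x 0.9 = 216. Normal quantiles: 1.960 and 1.2816.

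**1. Which comparison gives 720?** Pooled-variance formula for two proportions, dropout as N/(1 - 0.10).

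- *Minimally invasive arms pooled, 2:1 against craniotomy.* Mean rate (0.33 + 2 x 0.21)/3 = 0.25. Craniotomy n = [1.960 x sqrt(0.25 x 0.75 x 1.5) + 1.2816 x sqrt(0.33 x 0.67 + 0.21 x 0.79/2)]^2 / 0.12^2 = (1.0394 + 0.7067)^2 / 0.0144 = 211.7, so 212. Total 212 + 424 = 636; 636/0.9 = 707. This is 1.8% below 720.
- *Each technique against craniotomy, 1:1.* Mean rate 0.27. n = [1.960 x sqrt(2 x 0.27 x 0.73) + 1.2816 x sqrt(0.33 x 0.67 + 0.21 x 0.79)]^2 / 0.0144 = (1.2306 + 0.7972)^2 / 0.0144 = 285.6, so 286 per arm; 286/0.9 gives 318 per arm, 954 in total.
- *Three-group test, 2 df, rates 33/21/21.* Noncentrality = n x sum(p_i - 0.25)^2 / (0.25 x 0.75) = n x 0.0096/0.1875 = 0.0512n. Power of 90% needs 248 per arm, or 276 after dropout, 828 in total.

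One-sided, continuity-corrected, unpooled and arcsine versions of the pairwise calculation also miss 720 at 90% power (259 to 336 per arm after dropout). A pairwise two-sided calculation at 80% power gives 238 per arm, 714 in total, but the protocol states 90%.

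**2. Power at 216 evaluable per arm, rates 33/21/21.** Pooled 90.5%; three-group test 85.5%; each technique against craniotomy at .05, 80.4% by formula and 80.7% by simulation.

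**3. False positives when all three rates are equal.** Simulated binomial trials, 216 per arm, all at 33%:

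| Rule | Chance of at least one false positive |
|---|---|
| Three-group test alone | 5.0% |
| Two ungated tests against craniotomy, .05 each | 9.0% |
| Three ungated pairwise tests, .05 each | 12.1% |
| Three-group test, then pairwise tests only if significant | 5.0% |

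As a check, independent tests would give 1 - 0.95^2 = 9.75% and 1 - 0.95^3 = 14.3%. The values in the table are lower because the comparisons share arms.

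**4. What a significant three-group test means when one technique is inert (33/21/33).** Noncentrality = 216 x 0.0096/(0.29 x 0.71) = 10.07, which gives power of 81.8%; simulation of the binomial counts gives about 83%. With the gated procedure, the inert technique is declared different from craniotomy in 4.9% of trials.

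**5. Cost of gating, rates 33/21/21, 216 per arm (simulation).** Power per technique 76.9%, against 80.7% ungated and about 72% with a Bonferroni split over two comparisons. Both techniques are shown in 69.3% of trials.

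**The case against.** A reader might infer that the protocol plans uncontrolled pairwise testing with a 9 to 12% error rate. The text does not support that: it mentions neither separate tests nor a three-group table, and those figures follow only from one open reading. Under the pooled reading, which fits the sample size best, there is a single test at 5%. The 12.1% also leans on a softer aim, since finding the best method is worded as something that the trial will help with; for the primary aim the figure is 9.0%.

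Gating and multiplicity detail are often left to a statistical analysis plan, and one may exist that settles them. Statisticians also disagree on whether distinct treatments sharing a control need adjustment at all. Finally, the Statistical analysis section plans relative risks and a logistic regression that includes surgical method, so technique-specific estimates are likely to be available.

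These points remove any claim that the protocol has committed to an inflated error rate. They do not remove the mismatch. The protocol itself states the primary test, the objective and the sample size, and they do not describe the same comparison. The regression is not the primary test. The protocol also claims a type I error of .05 while asking about two techniques and a best method, so its own claim needs a rule.

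**Conclusion.** The point holds as a mismatch between the primary test, the objective and the sample size, and should be fixed. The three-group and pooled readings keep 5% but do not identify a technique; with one inert technique the three-group test is still significant in about 83% of trials, so it cannot be read as support for both. Separate ungated tests identify a technique, but at about 9.0% (two comparisons) or 12.1% (three), not .05. The stated 90% power belongs, at 720 patients, to the pooled comparison; for each technique against craniotomy it is about 80%.

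These figures assume the protocol's rates, exactly 10% dropout in every arm (216 evaluable) and one final analysis. The 83% further assumes one technique at the craniotomy rate of 33%, which is an illustration and not a protocol assumption.

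**What to change.** State the primary analysis as a closed procedure:

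1. Three-group Chi-squared test of unfavorable outcome at 6 months, two-sided .05.
2. Only if it is significant: endoscopic evacuation against craniotomy, aspiration against craniotomy, and endoscopic evacuation against aspiration, each at two-sided .05.
3. Report each risk difference with a 95% confidence interval, and make claims technique by technique.

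With exactly three groups this needs no alpha split and keeps the familywise error at 5% at the final analysis. The interim analyses mentioned under Data monitoring and quality control need their own boundary.

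The text costs a few sentences. The statistical cost is about 4 points of power per technique (80.7% to 76.9%), and showing both succeeds in about 69% of trials. The Sample size section should therefore restate power for these comparisons in place of 90%. If 90% per technique is wanted, even ungated testing needs 954 patients, and gating needs somewhat more.

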**Study design**

This is a multicenter, randomized, controlled, open-label, sequentially designed non-profit study (ClinicalTrials.gov ID: NCT02811614) involving 16 neurosurgical centers. Patients with newly diagnosed supratentorial HICH according with our inclusion criteria will be enrolled in this study. A follow-up period of 6 months will be sufficient enough to show outcome and prognosis of surgical treatment. A flowchart of this study is shown in Figure 1.

[figure not shown]

Figure 1 Flow chart of the study design

The trial will be conducted in the departments of neurosurgery at 16 Chinese hospitals: (1) Chinese PLA General Hospital, Beijing; (2) Jingzhou Central Hospital, Hubei province; (3) Wuhan No.1 Hospital, Hubei province; (4) Jinzhou Central Hospital, Liaoning province; (5) Yichang Central People’s Hospital, Hubei province; (6) Hainan Hospital of Chinese PLA General Hospital, Hainan province; (7) Liaoning Thrombus Hospital, Liaoning province; (8) Jiangmen Central Hospital, Guangdong province; (9) People’s Hospital of Sanshui District. Foshan, Guangdong province; (10) Minzu Hospital of Guangxi Medical University, Guangxi province; (11) The Second Hospital of Jilin University, Jilin province; (12) Jilin Province People’s Hospital, Jilin province; (13) Siping Central People’s Hospital, Jilin province; (14) Tangdu Hospital of Air Force Military Medical University, Shanxi province; (15) The Third Affiliated Hospital of Inner Mongolia Medical University, Inner Mongolia; (16) The First Affiliated Hospital of Xinjiang Medical University, Xinjiang province. All neurosurgeons taking part in the MISICH study have been trained by an annually held national continuing education program by Chinese PLA General Hospital about endoscopic evacuation, stereotactic aspiration, and small boneflap craniotomy. These three surgical techniques have been routinely used in all centers prior to the start of trial.

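### The primary Chi-squared test is valid but leaves out baseline prognostic data the trial already collects, and the only adjusted model planned conditions on a post-randomisation outcome

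*Protocol*

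**What the plan says.** The Statistical analysis section of the protocol fixes the primary test: "The primary analysis will be a simple categorical frequency comparison using the Chi-squared test". It is applied to the six-month result, split into favorable and unfavorable, where unfavorable means mRS 3-6 (Outcomes measurements).

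The same section plans a second analysis: "Logistic regression analysis will be undertaken for age, gender, hematoma volume, preoperative GCS, surgical method, and intracranial infection". It is not called primary. Intracranial infection during hospitalization is listed among the secondary outcomes under Outcomes measurements.

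Eligibility covers ages 18 to 80, GCS of 5 or more, and hematoma volume of 25 mL or more with no upper limit. Data collection and follow-up has demographic, clinical and neurological data recorded at enrolment, and preoperative hematoma volume measured in software.

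Patients are allocated "in 1:1:1 ratio using a central randomization system based on computer-generated number sequence". No stratification factor is mentioned.

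The sample size rests on raw proportions, 33% falling to 21%, and the text reads: "A sample size of 720 (240 in each group) would be required to show a 12% benefit from minimally invasive surgery". The target power is 90% at a type I error of .05, and an allowance of 10% is made for dropout.

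**The concern.** Age, level of consciousness and hematoma volume can be expected to affect six-month outcome after intracerebral hemorrhage, and the protocol treats them as relevant by naming them as model terms. An unadjusted test leaves the variation they explain in the error term. Any chance imbalance in them also stays in the observed difference, where it adds noise but not bias.

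The planned logistic regression does not supply what is missing. Infection occurs after surgery, and the arms differ in exposure to it. The aspiration arm keeps a catheter with repeated urokinase for up to 5 days, urokinase is not given after endoscopy, and a catheter after craniotomy is placed only when needed. If technique affects infection and infection affects outcome, conditioning on infection can remove part of the treatment effect or distort it. The coefficient for surgical method then does not estimate the effect of being assigned to a technique.

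At stake are some power and a narrower confidence interval. The first objective asks whether, and to what extent, the two techniques improve outcome, so the precision of the effect estimate matters as well as the P value.

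**Working it through.** **Inputs.** From the protocol: 33% versus 21%, two-sided 0.05, 90% power, 240 per arm, 10% dropout. Evaluable per arm: 240 × 0.90 = 216. Assumed, because the documents give nothing: the share R² of outcome variance explained by age, GCS and volume, taken as 5-30%.

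**Step 1: reproduce the plan's 720.** With k comparison patients per craniotomy patient and p̄ the pooled rate,

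n = [1.960·√(p̄(1−p̄)(1+1/k)) + z_power·√(p1(1−p1) + p2(1−p2)/k)]² / (p1−p2)²

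- One technique versus craniotomy (k = 1, p̄ = 0.27): (1.960 × 0.6279 + 1.282 × 0.6221)² / 0.0144 = 286 per arm. Then 286/0.90 = 318, or 954 for three arms. The stated 240 does not reproduce at 90% power. At 80% power the formula gives 214, then 238, or 714 in total.
- Both minimally invasive arms pooled versus craniotomy (k = 2, p̄ = 0.25): (1.960 × 0.5303 + 1.282 × 0.5514)² / 0.0144 = 212 controls. Then 212/0.90 = 236, or 708 in total. This is within 2% of 720.

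**Step 2: power of the unadjusted test with 216 evaluable per arm.**

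Power = Φ{[0.12·√216 − 1.960·√(p̄(1−p̄)(1+1/k))] / √(p1(1−p1) + p2(1−p2)/k)}

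- Pairwise: (1.7636 − 1.2306)/0.6221 = 0.857, so 80.4%.
- Pooled: (1.7636 − 1.0394)/0.5514 = 1.313, so 90.5%.
- Three-arm Chi-squared test (33/21/21, 2 df): noncentrality 216 × (0.08² + 0.04² + 0.04²)/(0.25 × 0.75) = 11.06, so 85.5%.

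**Step 3: power after adjustment.** To a first approximation, adjustment multiplies the variance of the standardised risk difference by (1 − R²), which acts like 216/(1 − R²) patients per arm.

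| Assumed R² | Effective n per arm | Pairwise power | Pooled power |
|---|---|---|---|
| 0 | 216 | 80.4% | 90.5% |
| 5% | 227 | 82.4% | 91.9% |
| 10% | 240 | 84.4% | 93.1% |
| 20% | 270 | 88.3% | 95.5% |
| 30% | 309 | 92.1% | 97.4% |

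**Step 4: cross-check by simulation.** Logistic regression on arm and three baseline covariates was simulated with the marginal rates held at 33% and 21% (6,000 trials pairwise, 3,000 pooled; Monte Carlo error about half a point). Discrimination of the covariates is again an assumption.

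| AUC of covariates | Pairwise, unadjusted → adjusted | Pooled, unadjusted → adjusted |
|---|---|---|
| 0.50 | 80.7% → 80.5% | 91.5% → 91.4% |
| 0.63 | 80.3% → 81.9% | 89.6% → 91.1% |
| 0.70 | 80.9% → 84.9% | 90.7% → 93.4% |
| 0.78 | 80.8% → 87.8% | 91.3% → 95.8% |
| 0.83 | 81.5% → 91.8% | 91.7% → 97.3% |

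The two methods agree in pattern. Useless covariates cost essentially nothing, weak ones add 1-2 points, and strong ones add about 10 points pairwise and about 6 pooled.

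**The case against.** The strongest reply is that nothing here is wrong. After 1:1:1 randomisation an unadjusted Chi-squared test controls type I error, and it matches a sample size built from two raw proportions. Chance imbalance is already allowed for in the test's error rate. An adjusted model is also planned, so the dispute is over which analysis carries the primary label. Most of this stands. It does not answer the infection term: as written, the plan offers an unadjusted test and a model conditioned on a post-randomisation outcome, and nothing between them.

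A reader might infer more than the documents support on two points.

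- *That the trial wastes power it needs.* This depends on the contrast, which the protocol does not name. The pooled contrast already reaches 90.5% unadjusted, and the three-arm test 85.5%. Only the pairwise contrast sits near 80%, and adjustment brings that above 90% only with strong covariates (AUC 0.83 in the simulation). No prognostic strength is given, so no single gain can be claimed.
- *That centre must be in the model.* The protocol names 16 centers but is merely silent on strata. Such detail may be in the statistical analysis plan, which is not at hand, and silence does not oblige centre adjustment.

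**Conclusion.** The point holds as a matter of precision, not validity. The protocol makes an unadjusted test primary although strong candidate covariates are collected at baseline, and its only adjusted model is compromised by intracranial infection. Under an assumed R² of 5-30% with 216 evaluable per arm, adjustment moves power for 33% versus 21% from 80% to 82-92% pairwise and from 90.5% to 92-97% pooled. At the weak end the gain is 1-2 points.

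These figures rest on the protocol's own event rates and dropout, and on a prognostic strength that the documents do not give. The infection term needs no assumption about size: the protocol itself lists infection as an outcome. Adjustment does not settle which contrast among the three arms is primary. That is a separate issue.

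**What to change.** Make the primary analysis a prespecified logistic regression of unfavorable 6-month outcome on surgical method, adjusted only for age, preoperative GCS and baseline hematoma volume. Leave intracranial infection out. Report standardised (marginal) risk differences or relative risks with 95% CI, so that the estimate stays on the scale used for the sample size. Keep the Chi-squared test as the unadjusted sensitivity analysis. Adjustment for centre and an ordinal analysis of the mRS are optional additions.

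The cost is a change of wording, slightly more analysis work, and a primary estimate that depends on a model. No further patients or data are needed. To be credible, the change should be fixed before outcome data by arm are seen.

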**Eligibility criteria**

***Inclusion criteria***

1. Men and women aged 18-80 years old

2. Present with supratentorial HICH confirmed by brain computed tomography (CT) scan, hematoma volume ≥25mL

3. Glasgow Coma Scale (GCS) score ≥5

4. Patients are admitted to the above-mentioned hospitals within 24 hours of ictus

5. Patients or their dependents (when patients in coma) provide written consent.

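### Day-7 GCS is to be compared by one-way ANOVA with no adjustment for the preoperative GCS that the trial already collects, which loses precision on a secondary outcome

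*Protocol*

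**What the plan says.** The Statistical analysis section of the protocol gives one rule for all quantitative outcomes: "The continuous variables will be analyzed by One-way ANOVA". It attaches no covariate, transformation or rank-based alternative. The only tests or models named anywhere are the chi-squared test (primary outcome), one-way ANOVA and logistic regression.

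The Outcomes measurements section lists among the secondary outcomes "operation time, intraoperative blood loss, postoperative GCS score 7 days after surgery", then days of NICU stay, and ends with "hospitalization expenses, and Barthel Index at 6 months".

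Preoperative GCS is available. Eligibility requires "Glasgow Coma Scale (GCS) score ≥5", and the same statistical paragraph states: "Logistic regression analysis will be undertaken for age, gender, hematoma volume, preoperative GCS, surgical method, and intracranial infection".

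For description, the paragraph leaves the choice open: "Measurement data will be described using mean and standard deviation or median and interquartile range".

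**The concern.** A patient's GCS before surgery is likely to predict the GCS a week later. An unadjusted comparison treats that predictable between-patient variation as noise. The protocol judges preoperative GCS important enough to enter in a regression, yet does not use it for the outcome that measures the same score again.

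The stake is limited but real. Day-7 GCS is an early measure of recovery under three operations, and the Objectives section wants to know which is best. A wider confidence interval than the data require makes a modest difference harder to see or to rule out.

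A second, weaker worry is that the one rule also covers operation time, blood loss, NICU days and expenses, which may be right-skewed. Tests on raw means can then have less power than tests on logs or ranks.

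**Working it through.** **Figures in the plan.** The protocol gives no power, SD, effect size or correlation for any continuous outcome, so there is no stated figure to reproduce on this point. Its only calculation (720 patients) concerns the binary primary outcome and is used here only for the number per arm: 240 × (1 − 0.10) = 216.

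**Inputs for day-7 GCS**
- From the protocol: 216 per arm, three arms, two-sided 0.05 ("A value of two side P <.05 was considered statistically significant").
- Assumed: correlation r of 0.3, 0.5 or 0.7 between preoperative and day-7 GCS within arms, with a linear relation.
- Assumed: both minimally invasive arms shifted by d = 0.25 SD from craniotomy.

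**Step 1: variance.** Adjustment leaves a share 1 − r² of the variance. The equivalent unadjusted size is n / (1 − r²), and the standard error is multiplied by √(1 − r²).

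| r | 1 − r² | Equivalent n per arm | SE factor |
|---|---|---|---|
| 0.3 | 0.91 | 216 / 0.91 = 237 | 0.95 |
| 0.5 | 0.75 | 216 / 0.75 = 288 | 0.87 |
| 0.7 | 0.51 | 216 / 0.51 = 424 | 0.71 |

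**Step 2: power.** The noncentrality of the three-arm F test is λ = n × Σ(μⱼ − μ̄)² / [σ²(1 − r²)]. With two arms shifted by d (in SD units), the sum is (2/3)d²σ². So without adjustment λ = 216 × (2/3) × 0.0625 = 9.0, and with adjustment λ = 9.0 / (1 − r²), that is 9.9, 12.0 and 17.6.

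| Shift d | ANOVA | ANCOVA r = 0.3 | r = 0.5 | r = 0.7 |
|---|---|---|---|---|
| 0.20 SD | 56.3% | 60.6% | 69.7% | 86.1% |
| 0.25 SD | 76.9% | 80.9% | 88.2% | 97.1% |
| 0.30 SD | 90.6% | 93.1% | 96.8% | 99.7% |

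**Step 3: skewed outcomes (conditional).** Simulation of log-normal data, 216 per arm. The contrast is one arm 25% higher or, equivalently, two arms 20% lower (1/1.25 = 0.8). Both versions were run. Log SDs are assumed.

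| Log SD | Contrast | Raw ANOVA | Log ANOVA | Kruskal-Wallis |
|---|---|---|---|---|
| 0.6 | one arm 25% higher | 96.7% | 98.4% | 98.1% |
| 0.8 | one arm 25% higher | 73.2% | 86.2% | 84.9% |
| 0.8 | two arms 20% lower | 73.7% | 85.3% | 83.8% |
| 1.0 | one arm 25% higher | 47.2% | 66.7% | 64.4% |
| 1.0 | two arms 20% lower | 47.9% | 67.2% | 65.1% |

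At log SD 0.8 to 1.0, logs gain about 12 to 20 points and ranks about 10 to 17. At log SD 0.6 the gain is under 2 points.

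With larger differences the gap closes. One arm 50% higher gives 99.7%, 100% and 100% at log SD 0.8, and 93%, 99% and 99% at 1.0. With one arm doubled, all three reach 100%. Under no difference, raw ANOVA rejected in 4.7% to 5.4% of runs in the version with two arms shifted.

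**The case against.** **No error is shown.** At more than 200 per arm, one-way ANOVA is a valid comparison of means and type I error holds. Only secondary outcomes are affected, and no stated power is missed because the protocol powers only the binary outcome. All of this stands, and it fixes the weight of the point.

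**This belongs in the SAP.** Covariates and fallback tests for secondary outcomes are often left to an SAP, which is not at hand. But the protocol does not stay silent: it names a method and allows no adjustment. That can be criticised as written.

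**GCS is an ordinal, bounded score and is never called continuous.** True, but the paragraph offers no other method for it. Requiring a score of at least 5 also narrows the baseline range, which may lower r. That is a reason to look at the low end of the range, not to leave the covariate out.

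**The number per arm is not exact.** The 10% dropout relates to follow-up, so an in-hospital measure may have nearer 240 per arm. The variance ratio 1 − r² does not depend on n. Deaths before day 7 also matter for this outcome, but are a separate question.

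**The skewness scenario favours the alternatives.** A multiplicative shift in log-normal data is where a log analysis does best. The three operations may differ greatly in operation time and blood loss, and then the choice of test changes nothing. Logs fail at zero, which is possible for blood loss, and logs or ranks change what is estimated. This stands, and it reduces that part to a conditional remark.

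**Conclusion.** The point holds for day-7 GCS. The protocol assigns an unadjusted test although the baseline value of the same score is collected and already used in another model. The loss at 216 per arm is equivalent to about 21, 72 or 208 patients per arm (237 − 216, 288 − 216, 424 − 216) at r = 0.3, 0.5 or 0.7. For a 0.25 SD shift it is about 4, 11 or 20 points of power. The correlations and the shift are assumptions; the documents offer nothing to choose among them. It is a minor, inexpensive improvement and not a flaw that threatens the trial.

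A reader might infer more, namely that ANOVA is invalid for skewed outcomes, that it should be replaced for every continuous variable, or that allowing medians in description contradicts testing means. The documents do not support these readings. They state no SD or skewness, the false-positive rate holds, and a median can describe a variable whose means are validly compared. For expenses the mean may well be the quantity wanted, and that is what ANOVA tests.

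**What to change.** **Day-7 GCS.** In the Statistical analysis section, exempt day-7 GCS from one-way ANOVA. Specify a linear model with treatment group (three levels) and preoperative GCS, reporting adjusted mean differences with 95% confidence intervals. Say which preoperative value is used. The one recorded at enrolment is preferable, because surgery may follow randomization by up to 12 hours and the surgeon by then knows the allocation.

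**Optional.** For operation time, blood loss and NICU days, pre-specify a rank or log-scale analysis beside the ANOVA, to be read if the data are heavily right-skewed. Ranks avoid the problem of zeros. Keep the comparison of means for expenses.

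**Cost.** One sentence, or two with the optional part, and one degree of freedom in the model. No new data, visits or patients are needed, and the named software can fit it. The optional analyses describe ratios or ranks instead of means, so they should be labelled as such. The wording should be settled before outcome data are seen, so that the choice of test is not made after the distributions are known.
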